### Sample size

A sample size of 5562 participants (2781 in the comparator group and 2781 in the intervention group) is required to detect a mean difference reduction of 2 UK units (16 g of alcohol) in weekly alcohol consumption (the primary analysis) at 90% power with an α of 0.05 and a two‐tailed test. This was calculated using G*Power software [22]. The estimated effect size is in line with the Cochrane review on digital alcohol interventions [5] and is roughly equivalent to that found in face‐to‐face brief interventions [23].

An initial sub‐sample of 26 participants (13 from each group [24]), who consented to a short interview about their experience of the trial, will be selected after the 6‐month follow‐up, as part of the mixed‐methods process evaluation. Participants will be purposively sampled to achieve good diversity in terms of sociodemographic characteristics and with high and low engagement. Data will be analysed and data collection will continue only if thematic ‘meaning’ saturation is not reached (see Analysis). Collection will continue in an iterative process (adding 10 participants at a time) until saturation is reached.

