#### Analysis of primary and secondary outcomes

The primary analysis will use a conservative intention‐to‐treat approach to missing data with the assumption of no change for participants who do not respond to follow‐up (i.e. analysis of outcome data from all randomised participants). The effect of group allocation on the primary outcome, change in weekly alcohol consumption, will be examined with an adjusted regression model, adjusting for baseline consumption [55, 56, 57].

A secondary analysis will be conducted to assess differences in change in weekly alcohol consumption using an unadjusted regression model. Regression models have several statistical assumptions that will be assessed (i.e. the errors of the data are normally distributed and there is equal variances between treatments). The analyses are robust to slight deviations in parametric assumptions, but where large deviations are found data transformations and appropriate non‐parametric tests will be considered.

Additional sensitivity analyses will be conducted for the primary outcome at 6 months: (i) responders‐only (i.e. those who completed the 6‐month follow‐up survey); (ii) using multiple imputation for non‐responders on baseline characteristics (with five imputed data sets [58] combined using Rubin's rules [59]) and assuming a normal distribution with a mean of 0 and SD reflecting the variation in change among responders; (iii) per‐protocol approach whereby only participants who downloaded Drink Less in the intervention group and those who viewed the NHS alcohol advice webpage in the comparator group are included in the analyses, and whereby participants whose treatment was contaminated are excluded; (iv) an instrument variable analysis accounting for non‐use in the intervention group and contamination in the comparator by operationalising the difference in app usage between the two conditions; (v) last observation carried forward; and (vi) assessing the effect of the condition by recruitment source.

Secondary analyses will assess: (i) the secondary outcomes at 6 months using ANOVA and χ^2^ analyses as appropriate and (ii) the change over time in the primary outcome using 1‐ and 3‐month follow‐up data.

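### The multiple-imputation sensitivity analysis centres non-responders' change on 0, so it repeats the primary no-change assumption instead of testing it

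*Protocol article*

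**What the plan says.** The primary analysis includes everyone randomised and makes the "assumption of no change for participants who do not respond to follow"-up. The effect of allocation on change in weekly units "will be examined with an adjusted regression model, adjusting for baseline consumption".

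Six sensitivity analyses of the 6-month outcome follow. The second is described as "using multiple imputation for non‐responders on baseline characteristics (with five imputed data sets", pooled by Rubin's rules), and the same sentence continues "assuming a normal distribution with a mean of 0 and SD reflecting the variation in change among responders". Two others bear on missing outcomes: (i) keeps only those who completed the 6-month survey, and (v) is "last observation carried forward". A secondary analysis of change over time uses the 1- and 3-month data, with no model stated. The Discussion accepts that the primary approach would, if anything, understate the effect.

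**The concern.** A missing-data sensitivity analysis is useful when it replaces the primary assumption with a different plausible one. Here the imputed quantity is change, and its mean is fixed at 0 for every non-responder, whatever their arm, baseline drinking or answers at 1 and 3 months. That is the primary assumption with random scatter added. If the two results agree, the agreement follows from the construction and says nothing about whether non-responders really stayed the same.

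The sentence also pulls two ways. Imputing from baseline characteristics means that the predicted value depends on them. A mean fixed at 0 means that it does not.

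This matters because (ii) is the only multiple-imputation check listed, and the article itself warns, under Primary outcome measure, that digital trials can suffer high attrition.

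**Working it through.** **Inputs from the article.** Primary analysis: change = 0 for non-responders in both arms. Analysis (ii): change drawn from a normal with mean 0 and the responders' SD, "five imputed data sets", Rubin's rules. Sample size: 2781 per arm to "detect a mean difference reduction of 2 UK units" "at 90% power with an α of 0.05". Response rates, the SD and the mean change in each arm are not given, so they are assumed below.

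**The plan's own figure.** Without an SD, 5562 cannot be rebuilt from the article alone. Solving n = 2·SD²·(1.960 + 1.282)²/2² backwards from 2781 gives SD = 23.0. With SD 23, the normal formula gives 2780 per arm and a t-test calculation gives 2781, that is 5562 in total. SD 22 gives 5086 and SD 24 gives 6054. SD 23 is used only to scale the simulation; steps 1 and 2 do not depend on it.

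**Step 1: expected estimates.** Let p_I and p_C be the response rates, and m_I and m_C the responders' mean changes.

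- Primary: p_I·m_I + (1 − p_I)·0 − [p_C·m_C + (1 − p_C)·0] = p_I·m_I − p_C·m_C.
- Analysis (ii): the draws have mean 0, so the expression is the same. Adjustment for baseline does not change this in expectation, because allocation is random.

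With equal response p, both give p × effect. With unequal response and no true effect, both give (p_I − p_C)·m. For example, with 80% against 75% and a common mean change of −8 units, 0.05 × (−8) = −0.40, a spurious benefit. A mean change of −4 gives −0.20 and −12 gives −0.60. Swapping the response rates reverses the sign. All of these values are assumed.

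**Step 2: standard error of (ii).** Let v = 2·SD²/n. Rubin's variance is about v[1 + 1.2(1 − p)], and the actual sampling variance of the pooled estimate is about v[p + (1 − p)/5]. At 80%, √(1.24/0.84) = 1.22.

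| Response (assumed) | Expected estimate, primary and (ii), true effect 2 | Rubin SE ÷ actual SE |
|---|---|---|
| 60% | 1.2 | 1.48 |
| 70% | 1.4 | 1.34 |
| 80% | 1.6 | 1.22 |
| 90% | 1.8 | 1.10 |

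**Step 3: simulation.** 600 trials per setting, 2781 per arm, SD 23, comparator mean change −8, true reduction 2, equal response:

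| Response | Primary | Analysis (ii) | Responders only |
|---|---|---|---|
| 70% | 1.38 | 1.39 | 1.98 |
| 80% | 1.60 | 1.60 | 2.00 |
| 90% | 1.78 | 1.78 | 1.98 |

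Within a single trial the primary and (ii) differed by 0.07 to 0.13 units on average, which is imputation noise. The simulated SE ratios were 1.42, 1.17 and 1.16 at 70%, 80% and 90%. With no true effect and 80% response, (ii) rejected in 2.2% of trials and the primary in 5.0%.

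**Step 4: the other reading.** Suppose that the mean-0 normal is only residual noise around a prediction from baseline characteristics. At 80% response, a prediction model with arm gives 2.00 with an SE ratio of 0.97. A model without arm still gives 1.60, because non-responders in the two arms then get the same predicted change.

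**The case against.** **The sentence may mean residual noise.** On that reading, with arm in the model, the dilution and the SE problem both disappear. A full analysis plan is promised before analysis, and imputation details commonly sit there. The article does not exclude this reading. However, it ties the SD to the variation in change and not to residuals, and arm is not a baseline characteristic, so the reading rescues (ii) only by adding a term that the sentence does not mention. A stated mean of 0 is also a rule that the article fixes, and not a detail that it leaves out.

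**Other analyses already give a contrast.** This largely stands. Responders-only does not assume zero change and would show 2.00 against 1.60 at 80% response. Adjusted for baseline, it is valid if missingness depends only on arm and baseline. A reader might infer that no planned analysis uses the 1- and 3-month answers. The article does not support that: last observation carried forward uses them, and so does the change-over-time analysis. The narrower statement holds: no stated missing-data analysis puts them in a missing-at-random model.

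**The standard error is defensible.** Zero-filling treats unobserved changes as known. Adding noise and pooling by Rubin's rules carries that uncertainty into the interval, and some statisticians would want this. A reader might infer from an incorrect standard error that false positives rise. The opposite is true: the error is conservative.

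**Nothing says that agreement will be presented as robustness.** That is correct. The point is only that agreement could not support such a statement about the no-change assumption.

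**Conclusion.** The point holds in this form: read literally, analysis (ii) has the same expectation as the primary analysis and cannot test its no-change assumption, and its zero mean contradicts the use of baseline characteristics. For a true 2-unit effect and equal response, both return 1.2 to 1.8 units as response runs from 60% to 90%. Calling this dilution assumes that non-responders would have shown the responders' effect. The bias under unequal response depends also on an assumed mean change. The equality of the two estimates needs none of these assumptions.

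The standard-error excess of about 10% to 50% is a secondary, conservative and arguable matter.

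A reader might infer that the trial's main result is compromised. It is not: this is one of six sensitivity analyses, and the primary estimate, its test and the sample size do not depend on it. The appropriate grade is should-fix.

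**What to change.** Rewrite sensitivity analysis (ii) before the analysis plan is finalised:

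- Delete the zero mean and the accompanying SD.
- Impute missing 6-month consumption under missing-at-random, from a model that includes arm, baseline consumption, the baseline characteristics and the 1- and 3-month consumption values. Derive change from the imputed value, fit the primary regression and pool by Rubin's rules.
- If a missing-not-at-random check is wanted, add explicit shifts to the imputed values, set separately by arm, and report the result across a stated range.

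More than five data sets, and predictive mean matching to keep consumption non-negative, are optional refinements. The cost is one sentence in the plan and routine code. No new data are needed, and the primary analysis does not change.

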#### Follow‐up assessments

Follow‐up assessments will be conducted 1, 3 and 6 months after baseline. The 6‐month follow‐up assessment will assess the primary and secondary outcome measures and psychological measures; the follow‐up assessments at 1 and 3 months will assess the self‐reported weekly alcohol consumption only. Participants will have up to 30 days to complete each survey to maximise data retention. Participants will be sent up to three automated emails with a link to a web‐based survey for the follow‐up assessments on days 0, 5 and 9. Participants who do not complete the web‐based follow‐up assessment will be sequentially offered opportunities to do so via phone (called once per day on days 10–17), mailed survey (on day 18) and by postcard (on day 30). Participants will be compensated with gift vouchers of up to £36 for completing the three surveys: £6 for the survey at 1 and 3 months; £12 at 6 months with an additional £12 if the 6‐month survey is completed within 24 hours.

At the 6‐month follow‐up, participants will indicate whether they are happy to be called for a short interview about their experience of the trial; there is no additional compensation for this telephone interview. Acceptability will then be measured after the 6‐month follow‐up via telephone interviews.

Participants will be asked whether they experienced any unexpected consequences, adverse events or other harms from participating in the study (in an open‐ended question at the 1‐, 3‐ and 6‐month follow‐up) and whether they have used any other forms of support for alcohol reduction (at the 6‐month follow‐up).

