
#### Primary outcome measure

The primary outcome measure is change between baseline and 6‐month follow‐up in self‐reported weekly alcohol consumption estimated over the last month, in UK standard units. Change in weekly alcohol consumption will be derived from the extended quantity‐frequency questions of the AUDIT [34], adjusting for heavy episodic use (question 3 of the AUDIT) and therefore allocating an individual to a category of consumption that is closest to their actual consumption. The AUDIT‐C questions exhibit similar sensitivity and specificity to the full AUDIT [35] and have demonstrated excellent reliability and responsiveness to short‐term change [36]. The extended AUDIT‐C is a variant of the AUDIT‐C, which has a greater range of response options (seven instead of five) on the quantity and frequency items, therefore improving the granularity of the information collected. This method of deriving alcohol consumption has been used in other trials [37, 38, 39, 40] and has high levels of agreement in levels of self‐reported consumption when compared with other retrospective daily diary measures [41]. This measure minimises response burden on participants because of its brevity, which is a critical issue in digital trials that have minimal contact with participants and can suffer from high levels of attrition [42].

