#### Secondary outcome measures

Change between baseline and 1‐ and 3‐month follow‐ups in self‐reported weekly alcohol consumption estimated over the last 1 and 2 months, respectively;Heavy episodic alcohol use (measured using AUDIT question 3) at 6‐month follow‐upProportion of hazardous drinkers (AUDIT score ≥8);Alcohol‐related problems or consequences and alcohol‐related injury (measured using the Alcohol Short Index of Problems) [43] at 6‐month follow‐up;Use of healthcare services (measured using the Service Use Questionnaire) [44, 45] at 6‐month follow‐up;Health‐related quality of life (measured using the EQ‐5D‐5L) at 6‐month follow‐up.

The self‐report AUDIT questionnaire has 10 items that measure alcohol consumption, harms and dependence. The AUDIT is a reliable and standardised alcohol‐related outcome measure that is commonly used in alcohol trials [5, 23]. It has a high test–retest reliability when completed online [46], allows the derivation of a core outcome set for consistency across trials and minimises research waste and selective reporting [47]. The timeframe of the AUDIT will be modified to refer to the past 6 months when asked at the 6‐month follow‐up so this can be directly compared with the baseline AUDIT, which will also refer to the past 6 months. The extended AUDIT‐C when asked at the 1‐ and 3‐month follow‐up will refer to the past 1 month and 2 months, respectively, to capture participants’ alcohol consumption since the last survey.

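### Last observation carried forward, sensitivity analysis (v), is a weak and partial check on the no-change rule; a repeated-measures model on the same data would serve better

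*Protocol article*

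**What the plan says.** Everything is in the protocol article. Under Analysis of primary and secondary outcomes, the primary analysis proceeds "with the assumption of no change for participants who do not respond to follow"-up; in effect, baseline is carried forward. The same section then says "Additional sensitivity analyses will be conducted for the primary outcome at 6 months" and lists six. Three of them concern missing data:

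- (i) responders only, meaning "those who completed the 6‐month follow‐up survey";
- (ii) multiple imputation on baseline characteristics, "assuming a normal distribution with a mean of 0 and SD reflecting the variation in change among responders";
- "v) last observation carried forward".

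The other three are the per-protocol, instrumental-variable and recruitment-source analyses.

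Interim values exist to be carried: "Follow‐up assessments will be conducted 1, 3 and 6 months after baseline" (Follow-up assessments). Their recall periods "will refer to the past 1 month and 2 months, respectively" (Secondary outcome measures), whereas the primary outcome is "weekly alcohol consumption estimated over the last month, in UK standard units" (Primary outcome measure).

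The section also plans a secondary analysis of change over time with the 1- and 3-month data and does not name its model. The article gives no expected response rate and no reason for choosing (v).

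**The concern.** A sensitivity analysis for missing data should replace the primary assumption with a different and plausible one. Item (v) does so for only some participants, and the replacement is hard to defend.

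For those never followed up, it leaves the primary assumption untouched. For those last seen at 1 or 3 months, it assumes that the change seen then persisted to 6 months. It treats the carried value as an observed outcome, so uncertainty is understated. A value carried from month 3 also covers two months of drinking rather than one.

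This matters because the Discussion names retention as one of two main challenges and argues that the primary approach can only understate the effect. The supporting analyses should be able to test that claim. Agreement between the primary result and (v) may mean only that few participants were partial responders. Disagreement may mean only that an early effect faded.

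**Working it through.** **Inputs.** From Sample size: 2781 per arm, target difference 2 units, 90% power, two-sided α 0.05. The rest are assumptions, because the article gives no such figures:

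- 75% of participants complete, 7.5% are last seen at month 1, 7.5% are last seen at month 3, and 10% are never seen;
- drop-out is unrelated to outcome within arm;
- any common fall in consumption is the same at every visit.

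**1. The plan's own figure.** The SD is not stated. Solving back, SD = 2 / [(1.960 + 1.282) × √(2/2781)] = 23.0. With SD 23 a two-sample t-test needs 2781 per arm, so the stated size fits an SD of about 23. The standard error of the difference is then 23 × √(2/2781) = 0.62 units.

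**2. How the two rules differ.** Let R be the share responding at 6 months, f the share of non-responders with an interim value, and t the arm difference in those interim values. Let the difference among responders be 2 units.

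- No change: 2R
- Carried forward: 2R + (1 − R) × f × t
- Gap: (1 − R) × f × t

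| R | f | t | No change | Carried forward | Gap |
|---|---|---|---|---|---|
| 0.80 | 0 | any | 1.60 | 1.60 | 0 |
| 0.80 | 0.50 | 2 | 1.60 | 1.80 | 0.20 |
| 0.70 | 0.50 | 2 | 1.40 | 1.70 | 0.30 |
| 0.60 | 0.75 | 3 | 1.20 | 2.10 | 0.90 |

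With no partial responders the two analyses are identical. In the last row, carrying forward exceeds the difference seen in responders.

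**3. An effect that fades.** Assume a benefit of 4 units at month 1, 2 at month 3 and 0 at month 6.

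- Equal drop-out: 0.075 × 4 + 0.075 × 2 = 0.45 units of benefit reported.
- 5 points more drop-out after month 1 in the app arm: 0.125 × 4 + 0.075 × 2 = 0.65 units.

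The true 6-month difference is 0. A missing-at-random model gives about 0 and so, in this scenario, does responders-only.

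**4. More never-responders in the app arm.** Assume no effect, a common fall of 7 units, and never-responders 15% against 10%, with 15% partial responders in each arm.

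- No change: −0.70 × 7 − (−0.75 × 7) = +0.35
- Carried forward: −0.85 × 7 − (−0.90 × 7) = +0.35
- Responders only: −7 − (−7) = 0

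The false signal is the difference in never-response times the common fall: 0.05 × 7. It is 0.25 for a fall of 5 units, 0.50 for 10, and nil if consumption does not fall.

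**5. The extra non-response among partial responders instead.** The app arm is now 70% complete, 20% partial and 10% never.

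- No change: +0.35, as before
- Carried forward: −0.90 × 7 − (−0.90 × 7) = 0

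Here (v) does expose the bias of the primary rule.

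**6. What the list covers.**

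| Analysis | Departs from no change on average? | Uses 1- and 3-month data? |
|---|---|---|
| (i) Responders only | Yes | No |
| (ii) Multiple imputation | No, as written: mean 0 | No: baseline characteristics |
| (v) Carried forward | Partial responders only | Yes, by assuming persistence |

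No row uses the interim data under missing at random.

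**The case against.** A reader might infer that (v) cannot test the primary assumption at all. The documents do not support that. Consumption is measured at 1 and 3 months, so for partial responders (v) replaces zero with an observed change. Step 5 shows a case where it reveals the bias of the primary rule.

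A reader might also infer that nothing in the plan uses the interim data properly. That is not established either. A change-over-time analysis is planned and its model is not named; the model may stand in the analysis plan, which is not among the documents. The 1- and 3-month changes are also secondary outcomes in their own right, so a fading effect would be visible there.

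Two further points are fair. The article does not present (v) as the sole test of the no-change rule: (i) drops that rule and, in step 4, gives the right answer. The sizes are also modest. Against a standard error of 0.62, biases of 0.35 and 0.45 are below one standard error, and 0.65 is about one. Step 4 depends wholly on an assumed fall.

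All of this stands, and it limits the point without removing it. Responders-only ignores the interim values, so it can be biased when drop-out depends on drinking at 1 or 3 months. Carrying forward uses them, but only by assuming persistence. The list offers nothing between the two.

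**Conclusion.** The point holds as an inexpensive improvement. Item (v) repeats the primary rule for participants never followed up and assumes persistence for the rest, so it is a weak, partial and sometimes misleading check.

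Under the stated assumptions it reports 0.45 to 0.65 units, roughly 0.4 to 0.7, for an effect that has vanished by month 6. That is up to about a third of the 2-unit target. Where one arm has 5 points more never-responders, it shares a false difference of about 0.35 units with the primary analysis, if consumption falls by 7 units in both arms. The response pattern, the fading effect and the common fall are all assumed, and the sizes scale with them. The primary estimate and its test are not affected by this point.

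**What to change.** Replace (v) with a mixed model for repeated measures fitted to change at 1, 3 and 6 months. It should have unstructured covariance, arm by visit, and baseline consumption by visit, and report the 6-month contrast between arms. Each visit has its own mean and variance, so the longer recall at month 3 need not be treated as equivalent to that at month 6. The same model can serve the planned change-over-time analysis.

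The cost is a few lines in the analysis plan, which the article says is to be finalised before analysis begins, and slightly more analysis work. No new data are needed. The drawback is reliance on missing at random: participants with no follow-up are handled through baseline consumption and arm alone, so the result should be read beside the primary analysis, which stays as it is.

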**Measurements:**

The primary outcome is change in self‐reported weekly alcohol consumption, assessed using the extended AUDIT‐Consumption, between baseline and 6‐month follow‐up. Secondary outcomes include change in self‐reported weekly alcohol consumption assessed at 1‐ and 3‐month follow‐ups, and the proportion of hazardous drinkers; alcohol‐related problems and injury; health‐related quality of life; and use of health services assessed at 6‐month follow‐up. Effectiveness will be examined with adjusted regression models, adjusting for baseline alcohol consumption and using an intention‐to‐treat approach. A mixed‐methods process evaluation will assess engagement, acceptability and mechanism of action. Economic evaluations will be conducted using both a short‐ and longer‐term time horizon.

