**Figure 2 add15287-fig-0002:**
[figure not shown]
Flowchart of procedure

**Table 1 add15287-tbl-0001:** Schedule of enrolment and follow‐up assessments

Assessment	Time‐point			
	Baseline	1 month	3 months	6 months
Informed consent	x			
Eligibility screening	x			
Randomisation	x			
Intervention/comparator initiation	x			
Sociodemographic characteristics^a^	x			
Weekly alcohol consumption	x	x	x	x
AUDIT score and proportion of hazardous drinkers	x			x
Alcohol‐related problems or consequences and alcohol‐related injury				x
Use of healthcare services				x
Health‐related quality of life				x
Psychological measures	x			x
Engagement	x	x	x	x
Acceptability				x
Adverse events		x	x	x
Debriefing				x

^a^

Sociodemographic characteristics include: age, sex, ethnicity, education, occupation, income.

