Confidence intervals, effect sizes (partial η^2^ for ANOVA analyses, odds ratios for χ^2^ and regression analyses) and exact *P* values will be reported. Bayes factors will be calculated using a half normal distribution to specify the predicted effect (of a 2 UK unit reduction per week) with a peak at 0 (no effect) and the SD equal to the expected effect size with Robustness Regions reported to specify the range of expected effect sizes that support the same conclusion [60].

Finally, interactions will be assessed between group allocation with age, sex, ethnicity, education, occupation, income and COVID‐19 measures (survey and national responses) for primary and secondary outcomes. Where significant interactions are found the findings will be stratified, drawing on the PROGRESS‐Plus framework to explicitly consider health equity between the intervention and comparator group [61].

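### The 6-month secondary outcomes are assigned to ANOVA and chi-square with no baseline covariate, which gives up some precision, and odds ratios are listed for a primary regression that yields a mean difference

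*Protocol article*

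**What the plan says.** All references are to the protocol article.

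- **Primary model** (Analysis of primary and secondary outcomes): the effect of allocation on change in weekly consumption "will be examined with an adjusted regression model, adjusting for baseline consumption". The section then discusses normal errors and equal variances, so this is a linear model of a continuous outcome.
- **Secondary outcomes** (same section): "the secondary outcomes at 6 months using ANOVA and" chi-square analyses, as appropriate. No covariate is named.
- **Effect sizes** (same section): partial eta squared for ANOVA and "odds ratios for χ^2^ and regression analyses".
- **Abstract, Measurements**: after listing primary and secondary outcomes it says "Effectiveness will be examined with adjusted regression models, adjusting for baseline alcohol consumption".
- **Table 1**: the row "AUDIT score and proportion of hazardous drinkers" is marked at baseline and 6 months, and weekly consumption at all four time points. Alcohol problems and injury, service use and quality of life are marked at 6 months only.
- **Secondary outcome measures**: heavy episodic use is AUDIT question 3. The AUDIT has a 6-month recall at both baseline and follow-up, so that the two can be compared.

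**The concern.** The trial collects the variables most likely to predict two of its secondary outcomes and then names tests that leave them out. Everyone enters with AUDIT ≥8 (Participants), so how far above 8 a person starts plausibly influences whether that person is below 8 at month 6. A two-by-two chi-square test ignores this. The same holds for heavy episodic use, whose own baseline is question 3. What is at stake is wider confidence intervals and lower power than the data allow.

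The effect-size list raises a second problem. Taken literally, it asks for an odds ratio from the primary regression, which cannot produce one. The quantity on which the trial is powered is not in that list.

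**Working it through.** **1. Is the secondary analysis unadjusted?** For chi-square, yes: the test has no place for a covariate. For ANOVA it is an inference. The Analysis section uses one-way ANOVA for baseline comparisons, with Kruskal-Wallis as fallback, and neither takes a covariate; but the sentence on secondary outcomes does not say one-way. The same section also plans interactions of group with age and other factors for the secondary outcomes. Age is continuous (Sociodemographic measures), so for a binary outcome that needs a regression model which the section does not name.

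**2. The plan's own figure.** The Sample size section gives 5562 participants, 2781 per arm, for 2 units per week, "at 90% power with an α of 0.05 and a two"-tailed test. The SD is not stated.

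- Formula: n per arm = 2(z₀.₉₇₅ + z₀.₉₀)² SD² / δ², with (1.960 + 1.282)² ≈ 10.51.
- Solving 2781 = 2 × 10.51 × SD² / 4 gives SD ≈ 23.0 units, a standardised difference of 2/23 = 0.087.
- With SD 23, the normal formula gives 2780 per arm and the exact t calculation gives 2781, total 5562.

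Because the SD was back-solved, this shows consistency only. It does confirm that the powered quantity is a mean difference in units. No sample size is stated for the secondary outcomes.

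**3. Size of the loss for AUDIT ≥8.** The article gives neither the correlation (rho) between baseline and 6-month scores nor the expected proportion ≥8 in the control arm, so both are assumptions. Simulation: 2781 per arm, complete data, 600 runs per setting; normally distributed baseline score; latent normal 6-month score with correlation rho, cut to give the stated proportion; effect chosen for about 80% chi-square power. Each data set was tested by chi-square and by logistic regression with the baseline score.

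| rho | Control ≥8 | Intervention ≥8 | Chi-square power | Adjusted logistic power | Gain (points) |
|---|---|---|---|---|---|
| 0.3 | 90% | 87.6% | 79.7% | 81.0% | 1.3 |
| 0.3 | 80% | 76.9% | 81.8% | 82.3% | 0.5 |
| 0.5 | 90% | 87.6% | 80.0% | 85.8% | 5.8 |
| 0.5 | 80% | 76.9% | 80.0% | 84.5% | 4.5 |
| 0.7 | 90% | 87.6% | 78.8% | 89.2% | 10.3 |
| 0.7 | 80% | 76.9% | 78.3% | 91.8% | 13.5 |

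The Monte Carlo standard error of one power figure is about √(0.8 × 0.2 / 600) = 1.6 points, so the gain at rho 0.3 is close to nothing and that at 0.7 is material.

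**4. The other secondary outcomes.** Heavy episodic use has its own baseline in question 3, but it is a single item, so the gain depends on the model used for its scale. Alcohol problems and injury, service use and EQ-5D-5L have no baseline of their own. Only baseline AUDIT score and consumption could be used, and the gain is likely smaller.

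**5. The effect measure.** The primary model has the form: change in units = a + b × group + c × baseline consumption + normal error. Its treatment effect b is a difference in mean change, in units per week. There is no event and hence no odds. An odds ratio would fit a logistic model, but the section names none.

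**The case against.** **The tests are valid.** Randomisation keeps the unadjusted comparisons unbiased, and the nominal error rate already allows for chance imbalance, which should be small with 2781 per arm. This stands. A reader might infer that the secondary results would be biased; the article gives no ground for that.

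**The gain could be overstated.** A reader might apply the usual factor for a continuous outcome, 1 − rho². At rho 0.5 it is 0.75 and at 0.7 it is 0.51, equivalent to 33% (1/0.75) and 96% (1/0.51) more participants. The article does not support that here. No 6-month secondary outcome is clearly continuous with its own baseline: AUDIT ≥8 is binary, heavy episodic use is one item, and the other three are measured at 6 months only. Total AUDIT score is not a listed secondary outcome, and consumption at 1 and 3 months is handled under a separate item.

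**Covariates may be left to the analysis plan.** That is fair for ANOVA, where the wording leaves room and partial eta squared would fit a model with further terms. It is weaker for chi-square, because the article names a test that cannot adjust.

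**The abstract may only summarise the primary model.** It names baseline consumption, which is exactly the primary covariate. This reading is reasonable, so the mismatch is an ambiguity rather than a clear contradiction.

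**The odds-ratio wording may be a slip.** The planned interactions imply logistic models for binary outcomes, where odds ratios belong. The required confidence intervals, and Bayes factors for a 2-unit reduction, need the mean difference. So a reader should not infer that the primary result would go unreported. The stated effect measure still does not fit the only regressions described.

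**Conclusion.** The point holds on both parts, at moderate weight.

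The secondary plan is valid but less precise than the collected data allow. For AUDIT ≥8, about 80% power with chi-square becomes roughly 81–92% with adjustment. This rests on assumed correlations of 0.3–0.7, an assumed control proportion of 80–90%, a latent normal model and complete follow-up. Heavy episodic use should also benefit, by an amount not quantified here; for the remaining three outcomes the gain is likely smaller. That the ANOVA is unadjusted is inferred; that chi-square is unadjusted is certain.

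The effect-measure error needs no assumption: a linear regression of change in units gives a mean difference. It does not affect the primary test, only how its result is to be reported.

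**What to change.** In Analysis of primary and secondary outcomes, replace the ANOVA and chi-square sentence with:

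- AUDIT ≥8 at 6 months: logistic regression adjusted for baseline AUDIT score. The score is needed because hazardous status is the same for everyone at entry.
- Heavy episodic use: a model suited to its scale, adjusted for baseline question 3.
- Alcohol problems and injury, service use and EQ-5D-5L: regression suited to each outcome's type, adjusted for baseline AUDIT score and weekly consumption.

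In the effect-size sentence, give the adjusted mean difference in units per week with 95% confidence interval for the primary model, mean differences for other continuous outcomes, and odds ratios for binary outcomes only. Then make the abstract's sentence on adjusted regression agree with the analysis section.

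The covariates are already collected, so there is no cost in data or participants. The change does replace the named secondary tests, so it belongs in the analysis plan, which the article says will be finalised before analysis starts.
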